**Ethical Aspects**

All subjects will be informed of the study without knowing the real aim. They will sign the informed consent prior to their inclusion in the study. The study design will be conducted according to Helsinki Declaration.

**Allocation**

Patients will be randomly assigned to receive either physiotherapy or a surgical procedure. Concealed allocation is conducted using a computer-generated randomized table of numbers created prior to the start of the data collection by a clinical researcher not involved in the recruitment and/or treatment of patients. Individual and sequentially numbered index cards with the random assignment have been prepared. The index cards will be folded and placed in sealed opaque envelopes. A second researcher will open the envelope and proceed with treatment according to the group assignment. We will blind clinicians who obtain follow-up information to patient allocation.

**Physical Manual Therapy Intervention**

Patients allocated to the physical therapy group will receive 3 treatment sessions of manual therapies including desensitization maneuvers of the central nervous system of 30- minute duration, once/week. The techniques will include soft tissue mobilization and nerve/tendon gliding exercises. All physiotherapy treatment sessions will be applied by different therapists with 8 years of clinical experience working with this population each one.

The desensitization maneuvers include manual techniques directed at anatomical sites of potential entrapment of the median nerve (19). The session will include soft-tissue manipulation, myofascial release, stretching, and cross-fiber friction over the muscular interfaces related to the median nerve: scalenes, pectoralis minor, bicipital aponeurosis, pronator teres, transverse carpal ligament, and palmar aponeurosis. All these muscular interfaces are explored by the clinician and treated according to the following findings: pain on palpation and reproduction of sensory or motor symptoms of the patients. Other interventions targeting the neck (lateral glides applied to the cervical spine) will be also applied.

Finally, passive nerve/tendon gliding exercise targeted to the median nerve will be applied (20). This intervention intends to produce a gliding movement of the nerve and tendon in relation to their adjacent soft muscle tissues and involves the application of joint movements to the targeted structure proximally while releasing movement distally, followed by a reverse combination (21). The sequence of the nerve/tendon gliding exercise will be as follows: shoulder girdle depression, gleno-humeral abduction and lateral rotation, supination of forearm, wrist, thumb, and finger extension. In this position, concurrent elbow flexion and wrist extension is alternated dynamically with concurrent elbow extension and wrist flexion. The therapist alternates the combination of movement depending on the tissue resistance. Speed and amplitude of movement are adjusted such that no pain was produced during the technique. The intervention will be completed over 5-10 minutes in 2 sets of 5min each with 1-min rest between sets.

The third last treatment appointment will include an educational teaching session of the tendon/nerve gliding interventions for doing as homework if necessary. Patients will be asked for not modifying any work or activity levels.

**Standardization of the Physical Manual Therapy Intervention**

We will standardize the physical manual therapy intervention to be homogeneous in the management of the patients. Prior to initiation of recruitment, a professional panel of physical therapists will develop the manual therapies to be included in the protocol and a detailed standardized document. This document will be used as coadjutant help during the sessions that physical therapists will receive as training. [name] will conduct the training sessions with two assistants before starting the study collection to perform quality assurance.

**Surgery intervention**

Patients randomly allocated to the surgery group will undergo open or endoscopic decompression and release of the carpal tunnel according to international guidelines. For pragmatic reasons and because no clear evidence supports any particular surgical procedure, surgery will be conducted based on surgeon’s and patient’s preference (22) All surgeons are highly experienced with at least 15 years of practice and habitual practices focusing on hand surgery. Surgeons will refer patients for hand therapy after operation as their usual routine if necessary. Patients allocated to this group will also receive the same educational session for performing the tendon/nerve gliding exercises as the physiotherapy group.

**Outcome Measures**

Clinical records of all patients will include questions regarding the location of the symptoms, aggravating/relieving factors, intensity, duration of the pain and previous treatments. They also complete the BDI-II for assessing symptoms of depression. The outcomes include pain, function, symptoms severity, and self-perceived improvement.

The intensity of pain will be assessed with an 11-point Numerical Pain Rating Scale (NPRS, 0: no pain; 10: maximum pain) (23). We will assess the patients’ current level of pain and the worst level of pain experienced in the preceding week. Farrar et al determined that a change of 2 points or a 30% decrease in pain intensity from baseline can be considered as a minimal clinically important difference (MCID) for the intensity of pain in patients with chronic conditions (24). For patients with bilateral symptoms, we designated the study hand on the basis of the more self-reported symptomatic hand; if symptoms were equivalent, the mean pain of both hands was considered.

The Spanish version (25) of the Boston Carpal Tunnel Questionnaire (26) (BCTQ) will be used to assess function and severity of the disease. This questionnaire evaluates 2 domains: a) the functional status scale assessing ability to perform 8 common hand-related tasks; b) the symptom severity scale including 11 items assessing pain severity, numbness, and weakness at night and during the day. Each question is answered on a 5points scale (1: no complaint; 5: severe complaint). Higher scores indicate greater severity or worse function. This questionnaire has been shown to be valid, reliable, and responsive for individuals with CTS (27). A change of 0.74 points in the function subscale and 1.14 points in the symptom subscale can be considered as MCID of the BCTQ (28).

Finally, self-rated improvement will be assessed with a Global Rating of Change (GROC), which consists of a 15-point scale ranging from -7 (a very great deal worse) to +7 (a very great deal better) (29).Descriptors of worsening or improving are assigned with values ranging from -1 to -7 and +1 to +7, respectively (30).It has been reported that scores of +4 and +5 are indicative of moderate changes in patient status, whereas scores of +6 and +7 indicate large changes in the status of the patient.

Pain and function will be assessed at baseline, and 1, 3, 6, and 12 months after the end of therapy, whereas GROC will be assessed at 6 and 12 months by an assessor blinded to the subject’s allocation.

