Before design a randomized clinical trial comparing the effectiveness of physical therapy versus surgery, we should analyze current advances in pain neurophysiology in this condition. CTS has been primarily considered a peripheral neuropathy localized at the carpal tunnel; therefore, previous studies comparing the use of physiotherapy and surgery applied localized treatments, including exercises, mainly focused to the hand (4-7). In addition, most of the studies included in previous reviews have used physical modalities different to manual therapy, such as hand splints (9,10), or laser (11). The only trial including manual therapies, particularly exercises, into a multimodal treatment approach was that one conducted by Jarvik et al (8). Interestingly, this study only found small differences between surgery and conservative management (8).

Recent evidence suggests that CTS is a complex syndrome showing sensitization of the central nervous system (12,13). In fact, these sensitization mechanisms are independent of electro-diagnostic findings and seem to play a potential relevant role in the development of chronic CTS (14). The presence of these sensitization processes would have an impact on conservative interventions, particularly manual therapies that should be applied to these patients. This hypothesis would be supported by preliminary data suggesting that manual physical therapies can modulate sensitization mechanisms by integrating neurophysiology of pain into their rationale (15,16). No study has applied manual therapy interventions with this consideration in patients with CTS. We believe that a high quality randomized clinical trial comparing the effectiveness of this physical manual therapy approach and surgery would help to improve the conservative management of CTS.

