**Participants**

Women diagnosed with CTS from local regional Hospitals in Madrid (Spain) will be screened for eligibility criteria. Participants will be diagnosed according to both clinical and electrophysiological findings. To be eligible, patients should exhibit all the following signs: pain/paresthesia in the median nerve distribution, increasing symptoms during the night, positive Tinel sign, and positive Phalen sign. Symptoms should have for at least 12 months. Further, the electro-diagnostic examination had to reveal deficits of sensory and motor median nerve conduction according to international guidelines of the American Association of Electrodiagnosis, the American Academy of Neurology (AAEAAN) and American Physical Medicine and Rehabilitation Academy (APMR) (17). A median nerve sensory conduction velocity <40 mm/s and a median nerve distal motor latency >4.20 ms are considered as abnormal (17). Patients will be classified according to the classification of Padua et al (18):minimal (abnormal segmental-comparative tests only), moderate (abnormal median nerve sensory velocity conduction and distal motor latency), and severe (absence of median nerve sensory response and abnormal distal motor latency) CTS.

Participants will be excluded if they exhibit any of the following criteria: 1, any sensory/motor deficit in the ulnar or radial nerves; 2, age >65 years; 3, previous surgery or steroid injections; 4, multiple diagnoses on the upper extremity (co-existing cervical radiculopathy); 5, neck, shoulder, or upper extremity trauma; 6, systemic disease causing CTS (diabetes mellitus, thyroid disease); 7, musculoskeletal medical conditions, e.g., rheumatoid arthritis or fibromyalgia; 8, pregnancy; 9, depressive symptoms (Beck Depression Inventory, BDI-II>8 points); or, 10, male gender.

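### In women with bilateral symptoms, the hand scored for pain is chosen by self-report alone and need not be a hand that met the entry criteria

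*Protocol*

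**What the plan says.** Protocol, Participants. The clinical criteria are worded for the patient: "To be eligible, patients should exhibit all the following signs", followed by median-distribution symptoms, night worsening, Tinel and Phalen. Symptoms must have lasted at least 12 months. In addition, "the electro-diagnostic examination had to reveal deficits of sensory and motor median nerve conduction". No hand or side is named, and the text does not say that the signs and the conduction deficit must be in the same hand. The electrodiagnostic severity class is also assigned to the patient.

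Protocol, Outcome Measures, in the paragraph on the numerical pain rating scale (NPRS), for women with symptoms in both hands: "we designated the study hand on the basis of the more self-reported symptomatic hand". For ties: "if symptoms were equivalent, the mean pain of both hands was considered". Self-report is the only criterion. The paragraph does not say when the hand is fixed, or whether the rule also governs the Boston Carpal Tunnel Questionnaire (BCTQ).

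Protocol, Sample size determinations. Pain is the main outcome, planned on a difference of 2.0 points with SD 3.0, two-sided alpha 0.05 and 90% power: at least 50 per group, raised to about 60 for 15% dropout.

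**The concern.** Entry is judged at the level of the woman, and the main outcome is measured at the level of a hand. When both hands have symptoms, the protocol's rule for moving from one to the other ignores the entry criteria.

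Take a woman whose right hand meets every criterion and whose left hand has symptoms but lacks the required conduction deficit. If she reports the left as worse, it supplies her pain score. If she reports them as equal, her score is the mean of a qualifying and a non-qualifying hand. Both results follow from applying the rules as written.

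Two things are at stake. The trial would report on electrodiagnostically confirmed carpal tunnel syndrome while some scored hands were unconfirmed. And if such hands show less difference between surgery and manual therapy, the estimated contrast shrinks.

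**Working it through.** **Step 1: the two rules side by side.**

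| Item | Unit | Criterion | Section |
|---|---|---|---|
| Symptoms, night worsening, Tinel, Phalen, 12 months | patient | all required | Participants |
| Sensory and motor conduction deficits | patient | required | Participants |
| Severity class | patient | electrodiagnostic | Participants |
| Study hand, bilateral symptoms, unequal | hand | self-reported symptoms only | Outcome Measures |
| Pain score, bilateral symptoms, equal | mean of both hands | none further | Outcome Measures |

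No section requires the scored hand, or both hands in a tie, to show the signs or the conduction deficits. With only one symptomatic hand there is no choice to make, so the gap is confined to women with bilateral symptoms.

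**Step 2: the plan's own figure.** Normal approximation, two-sided:

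n per group = 2(1.960 + 1.282)² × 3.0² / 2.0² = 47.3, so 48 (49 with the t distribution). The plan states at least 50, which agrees to within 2. Dropout: 50 / 0.85 = 58.8, so 59, against about 60 stated. The sample size is not in dispute and serves only as a yardstick.

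**Step 3: share of scored hands that do not qualify (assumed).** The documents give neither the share of bilateral women nor the share whose worse hand fails a criterion. Assume 40% to 60% and 10% to 20%:

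- low: 0.40 × 0.10 = 4%, or 4.8 of 120 women
- high: 0.60 × 0.20 = 12%, or 14.4 of 120 women

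**Step 4: effect on the contrast.** Let f be the share of scored hands that do not qualify. Assume those hands show no between-group difference, which is the extreme case, and that the SD stays at 3.0. The expected difference is 2.0(1 − f). Power at 50 per group is Φ[2.0(1 − f) / (3.0 × √(2/50)) − 1.960], and √(2/50) = 0.20, so the denominator is 0.60.

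| f | Expected difference | Power, 50 per group |
|---|---|---|
| 0 | 2.00 | Φ(1.373) = 91.5% |
| 4% | 1.92 | Φ(1.240) = 89% |
| 10% | 1.80 | Φ(1.040) = 85.1% |
| 12% | 1.76 | Φ(0.973) = 83.5% |
| 20% | 1.60 | Φ(0.707) = 76.0% |

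A tied woman with one non-qualifying hand counts for about half in f: if one hand carries a difference of 2.0 and the other none, their mean carries 1.0.

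**The case against.** The strongest reply is that this is silence and not a contradiction. On an ordinary reading the signs and the conduction deficits describe the affected hand, and the Outcome Measures rule only settles the side in bilateral cases. Scoring the hand that the patient finds worse is defensible for a patient-reported pain outcome. Two entry criteria are themselves symptoms, so the worse hand will often be the qualifying one. And even the less favourable of the assumed cases in the 4% to 12% range costs about 8 points of power.

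Most of this stands, and it limits the size of the point. It does not remove it: the protocol states a selection rule for its main outcome, and that rule omits the link to eligibility.

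Stronger readings that a reader might infer are not supported:

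- **The protocol itself says that symptoms and conduction disagree between hands.** The Background says that "these sensitization mechanisms are independent of electro-diagnostic findings". That concerns sensitization. It does not compare one hand with the other or address self-reported symptoms.
- **The rule pushes the result towards the hypothesised similarity because decompression does little in a non-qualifying hand.** No statement in the protocol supports that mechanism. Dilution also presupposes a true difference, whereas the stated hypothesis is similar outcomes.
- **The groups are biased against each other.** If the hand is fixed before randomisation, the consequence is dilution only. The protocol does not state the timing and patients are unblinded, which is a reason to state it but no evidence of bias.
- **All patients and all outcomes are affected.** The rule covers women with bilateral symptoms and sits in the NPRS paragraph.
- **The analysis by severity is compromised.** The Statistical Analysis section does not use the severity class. The harm is only that a reader cannot tell which hand the class describes.

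**Conclusion.** The point holds for women with bilateral symptoms and for the NPRS pain outcome. The scored hand need not be one that met the entry criteria, and in a tie the averaged pain may include a hand that did not. This follows from the text and needs no assumption.

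The likely consequence is some dilution of the contrast and a blurred target population. The size cannot be derived from the documents and is probably small. The illustration of 1.92 to 1.76 points in place of 2.0, with power of about 89% to 83.5% against 91.5%, rests on assumed shares of bilateral and discordant women, on no treatment difference at all in non-qualifying hands, and on an unchanged SD. It shows an order of magnitude and is not an estimate. The point is a cheap improvement to the definition of the main outcome and does not threaten the trial's validity.

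**What to change.** In Participants, state that the inclusion criteria must be met in the study hand. In Outcome Measures, state that this hand is named before randomisation, as follows:

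- if only one hand qualifies, it is the study hand;
- if both qualify, the more symptomatic one is;
- the existing averaging rule for equal symptoms applies only when both hands qualify.

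Record the severity class for the study hand (for both hands where they are averaged), and say whether the same rule applies to the BCTQ.

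The cost is a few sentences and a field on the screening form, using examinations already done at screening. The downside is that in a few bilateral women the study hand will not be the one that bothers them most, and their baseline pain score may be lower, which leaves less room for improvement.

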**Blinding**

Subjects, treating physical therapist and surgeons will not be blinded to intervention assignment. The Principal Clinical Investigator, [name] PhD will be blinded to crossover information.

**Sample size determinations**

We determined two sample size determination based on pain and function outcomes. For pain intensity, sample size calculation was calculated to detect treatment differences of 2.0 units on pain (MCID), assuming a standard deviation of 3.0,a 2-tailed test, an alpha level (α) of 0.05 and a desired power (β) of 90%. The estimated desired sample size with pain intensity as the main outcome was calculated to be at least 50 subjects per group. A dropout rate of 15% was expected, so around 60 patients should be included in each group.

For function, sample size calculation was determined to detect between-groups treatment differences of 0.5 points (MCID) on function subscale, assuming a standard deviation of 0.7,a 2-tailed test, an alpha level (α) of 0.05 and a desired power (β) of 90%. The estimated desired sample size with function as the main outcome measure was calculated to be at least 45 subjects per group. A dropout rate of 15%-20% was expected, so around 60 patients should be included in each group.

We decided to include pain as the main outcome in this study for the following reasons: 1, pain within the median nerve-related areas is the most common symptom experienced by patients with CTS (31); 2, pain is mainly determined by the activity of peripheral nerve nociceptors and continuous nociceptive afferent bombardment from the nerve nociceptors can lead to central and peripheral sensitization mechanisms observed in these patients (32).

**Related logistical issues**

In both group, one researcher will call individuals by telephone every month for the first 3 months of the study to provide answer questions, to assess compliance with medical appointments (within the surgical group), and to identify adverse effects of interventions. After three months, the researcher will call participants each 2 months for the remainder of the follow up period (during 9 months), particularly for remember the consecutive appointments for the study.

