**PROTOCOL**

**Background**

Carpal tunnel syndrome (CTS) is the most common nerve entrapment of the upper extremity mainly featured by a compression of the median nerve at the carpal tunnel in the wrist. Papanicolaou et al reported a prevalence of 3.72% in the general American population (1). Women are most often affected reporting an annual incidence of 139 per 100,000 compared to 67 cases per 100,000 in males (women/men ratio 2:1) (2). The societal burden of CTS is substantial since these patients had several income lost due to pain (3).

Treatment approaches for individuals with CTS mainly include conservative or surgical procedures; however, their scientific evidence had exhibited conflicting results. For instance a recent Cochrane Review investigating the effectiveness of hand exercises concluded that there is limited and low quality evidence of the benefit for exercise and mobilisation interventions for CTS (4). Another Cochrane Review found that surgical treatment relieves symptoms significantly better than hand splinting; but more research is needed to determine whether this conclusion can be applied to people with mild symptoms and whether surgical treatment is better than steroid injection (5).

The most updated review comparing surgical versus conservative management showed that both approaches may be effective for CTS, but surgical treatment seems to be slightly superior, showing moderate effect sizes, than conservative interventions at long-term (6). In fact, Huisstede et al found that evidence supports the effectiveness of conservative interventions at short-term, but there is a lack of evidence on mid-term and long-term effects in CTS (7). Therefore, since most trials have included short-term effects of conservative treatments, high quality randomized clinical trials determining the efficacy of conservative interventions at mid-term and long-term results are needed. This assumption would be further supported by the fact that 61% of the individuals with CTS try to avoid surgery (8) and they typically prefer conservative management as first therapeutic option because of the higher rate of complications associated to surgery (6).

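### Asking about adverse effects is specified only for the monthly calls of the first 3 months, and the start of the call schedule is not defined

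*Protocol*

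**What the plan says.** The Protocol sets out telephone contact under *Related logistical issues*. In both groups, "one researcher will call individuals by telephone every month for the first 3 months of the study". Three purposes follow: answering questions, checking that surgical patients keep their medical appointments, and "to identify adverse effects of interventions". The next sentence changes both frequency and purpose. Contact becomes two-monthly for the 9 months that are left, and the purpose given for it is "particularly for remember the consecutive appointments for the study".

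No other section plans to identify adverse effects. *Outcome Measures* states: "The outcomes include pain, function, symptoms severity, and self-perceived improvement". It gives the visit schedule as "Pain and function will be assessed at baseline, and 1, 3, 6, and 12 months after the end of therapy", with the global rating of change at 6 and 12 months, all by an assessor blinded to allocation.

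*Surgery intervention* gives no time from allocation to operation. *Physical Manual Therapy Intervention* specifies three weekly sessions.

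**The concern.** Finding adverse effects is a named task only in the early calls. After month 3 the same researcher keeps calling, but the text gives those calls another main purpose and does not mention harms. One caller could go on asking and another could stop, and both would be following the Protocol. An analysis plan cannot repair this later, because it concerns what is asked and when.

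It matters here because the main hypothesis is that the two treatments give similar pain and function at all follow-up periods. If that is what the trial shows, the choice between them will turn largely on harms. The *Background* makes the link itself, saying of patients that "they typically prefer conservative management as first therapeutic option because of the higher rate of complications associated to surgery", and asks for mid-term and long-term evidence.

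Relevant exposure may also continue after month 3. Gliding exercises for home use are taught in both arms, and surgical patients may be referred for hand therapy. *Blinding* mentions crossover information, so crossover seems to be foreseen, and a late crossover operation could fall wholly in the period with no specified enquiry.

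A second, smaller problem is the clock. The early calls are counted in months of the study, the later ones are placed in the follow-up period, and the visits are counted from the end of therapy. The Protocol does not say whether these share a starting point.

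**Working it through.** **Inputs.** From *Related logistical issues*: monthly calls for 3 months, then two-monthly calls for 9 months. From *Outcome Measures*: visits to 12 months after the end of therapy. From *Physical Manual Therapy Intervention*: three weekly sessions, so about 2 weeks from first to last. The time to surgery is not stated; 0 to 12 weeks is assumed below for illustration only.

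**Step 1: the Protocol's own schedule.** 3 + 9 = 12 months, the same length as the outcome follow-up.

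**Step 2: share of contacts with a named harms purpose.**
- Early calls: months 1, 2, 3 = 3 calls, purpose named.
- Later calls: months 5, 7, 9, 11 = about 4 calls, purpose not named.
- By calls: 3 / (3 + 4) = 3 of 7.
- By months of the call schedule: 3 / 12 = 25% with the purpose named and 9 / 12 = 75% without.

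These shares describe the call schedule whichever clock is used. They describe the 12-month outcome follow-up only if both schedules start together.

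**Step 3: does the undefined start matter?** Three months is 3 × 365.25 / 12 / 7 = 13.0 weeks.

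*Reading A: calls start at the end of therapy, as the visits do.* Both arms have 13.0 weeks and 3 early calls after treatment. There is no difference.

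*Reading B: calls start at allocation.* Weeks of early-call coverage after treatment = 13.0 − weeks from allocation to the end of treatment.

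| Arm | End of treatment (weeks after allocation) | Weeks covered | Early calls after treatment |
|---|---|---|---|
| Physiotherapy, sessions starting at once | 2 | 11.0 | 3 |
| Surgery, assumed | 0 | 13.0 | 3 |
| Surgery, assumed | 4 | 9.0 | 3 |
| Surgery, assumed | 8 | 5.0 | 2 |
| Surgery, assumed | 12 | 1.0 | 1 |

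Under Reading B the surgical arm may have more coverage than physiotherapy (13.0 v 11.0 weeks) or much less (1.0 v 11.0), depending wholly on a wait that the Protocol does not give.

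**The case against.** The strongest reply is that silence is not a rule. The later calls are made by the same researcher to both arms, and the word describing their purpose marks a main aim without excluding others. Asking about harms after month 3 is neither specified nor forbidden. This stands. A reader might infer that harms are not sought at all in the last 9 months, or are recorded only if volunteered; the text does not say so. What it supports is that no enquiry is specified there.

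A reader might also infer that waiting for surgery cuts the surgical arm's coverage, lowers its complication count and so favours surgery. The documents do not support this. No wait is stated. Because 3 + 9 months equals the visit follow-up, and the 9 months are called the remainder of the follow-up period, the calls can as well be read as starting at the end of therapy, with no imbalance. Even with a clock from allocation, the direction is not fixed.

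Two further points have some force. The Protocol plans no between-arm or time-course comparison of harms, so no stated analysis is invalidated. Some persisting problems would also register as outcomes: the Boston symptom scale covers pain, numbness and weakness, and the global rating runs down to −7. These scores are not adverse-effect records, however, and do not identify what happened or whether it was attributed to treatment. The gap in collection remains.

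**Conclusion.** The point holds as a gap in specification. Identifying adverse effects is a named purpose of 3 of about 7 calls, covering 3 of the 12 months of the call schedule, and of no visit, while pain and function are followed for 12 months. Late harms in either arm may therefore go unrecorded, or be recorded unevenly between callers. The count of 7 assumes later calls at months 5, 7, 9 and 11.

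The start of the call schedule is undefined and worded differently from that of the visits. Post-treatment coverage could differ between arms if the calls start before treatment, but this is conditional, and neither its size nor its direction can be derived from the Protocol. The primary pain analysis is unaffected. This is a cheap improvement to safety ascertainment.

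**What to change.** In *Related logistical issues*:

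- State that the telephone researcher asks the same structured adverse-effect question in both arms at every scheduled call, including the two-monthly ones.
- Count the calls from the same treatment-anchored time point as the visits in *Outcome Measures*, and use one term for it in both sections.
- Keep the question with the telephone researcher. The blinded visit assessor should not ask it, because a description of a surgical complication would reveal the allocation.

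The cost is a wording change, slightly longer late calls and a few more events to record. The calls and the researcher are already in the plan.
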